## Abstract

**Background:**

Adoption of healthy lifestyle and compliance with cholesterol-lowering medication reduces the risk of cardiovascular disease (CVD). The use of digital tools and mobile technology may be important for sustaining positive behavioral change.

**Objective:**

The primary objective of this study is to evaluate the feasibility and acceptability of administering the Cholesterol CarePlan Web app developed by the American Heart Association aimed at improving lifestyle and medication adherence among patients prescribed cholesterol-lowering medication. The secondary objective is to assess the Web app’s efficacy.

**Methods:**

A prospective, observational feasibility study will be conducted to demonstrate whether the Web app may be successfully taken up by patients and will be associated with improved clinical and behavioral outcomes. The study will aim to recruit 180 study participants being prescribed cholesterol-lowering medication for at least 30 days across 14 general practices in London, England. Potentially eligible patients will be invited to use the Web app on a smartphone and visit general practice for three 20-minute clinical assessments of blood pressure, height, weight, smoking, and nonfasting cholesterol over 24 weeks. The feasibility of administering the Web app will be judged by recruitment and dropout statistics and the sociodemographic and comorbidity profile of consenting study participants, consenting nonparticipants, and all potentially eligible patients. Acceptability will be assessed using patients’ readiness to embrace new technologies, the usability of the Web app, and patient satisfaction. The efficacy of the Web app will be assessed by changes in medication adherence and clinical risk factors by levels of the Web app compliance.

**Results:**

This study is currently funded by the American Heart Association. Initial study recruitment will take place between February and July 2018 followed by patient follow-up. Patient level data will be obtained in January 2019. Data analysis will be completed by February 2019. Results will be submitted for publication in March 2019.

**Conclusions:**

The potential of an app to improve patients’ lifestyle and management of cholesterol may inform the design of a randomized controlled trial and the delivery of more effective CVD prevention programs.

**International Registered Report Identifier (IRRID):**

PRR1-10.2196/9017

## Introduction

### Background

Cardiovascular disease (CVD) is a major cause of disability and premature mortality worldwide accounting for a third of deaths annually in England [1,2]. CVD contributes considerably to the rising cost of health care and is estimated to cost the National Health Service (NHS) and the United Kingdom economy £30 billion annually [1]. Much of the CVD burden is largely preventable [3-5]. Behavioral modification in relation to physical activity, nutrition, smoking, and alcohol consumption, as well as adherence to cholesterol-lowering and blood pressure- lowering medication, is associated with a reduction in the risk of CVD [5]. Prescribing statins is important for the primary prevention of CVD [6-11]. With a lower threshold for statin prescription in the United Kingdom and the United States, many more people will be prescribed lipid-lowering drugs [12-14]. Despite statin therapy, many individuals remain at risk of CVD events owing to behavioral factors such as poor medication adherence and adoption of healthy lifestyles [15]. A combined approach to control cholesterol should include better medication adherence and changes to lifestyle.

Primary CVD prevention programs are increasingly delivered using digital tools and mobile technology [16]. Used in health promotion, digital interventions may enable patient-centered care with improved communication, greater responsiveness to patient needs, and shared decision making [17,18]. Research showed digital interventions to be effective in improving cholesterol levels, medication adherence, weight loss, physical activity, smoking cessation, hypertension, and self-management of diabetes mellitus [16,19,20]. Such research was limited to short message services (SMS) text messages. In contrast, smartphones may enable accessing sophisticated content, such as self-monitoring programs and educational videos, to help patients monitor their risk factors and educate themselves to improve lifestyle and medication adherence. Growing smartphone ownership in the United Kingdom in the adult population makes smartphones an attractive platform for health interventions [21]. Nonetheless, a lack of scientifically designed and tested interventions impedes the successful primary prevention of CVD [22]. Of more than 43,000 apps listed in the health and fitness category of Apple’s iTunes Store in 2014, almost half were misclassified or were loosely affiliated with health and fitness [22]. Of 710 cardiology-related apps available in 2013, very few were designed for CVD prevention [22]. In addition, few health-related apps were developed per evidence-based guidelines and had quantifiable benefit for improving clinical outcomes [22]. Health-related apps are not being rigorously evaluated for the acceptability, sustainability of engagement, and the impact on clinical risk factors [16]. Good compliance with smartphone apps was described as content completion ranging from 69% to 72% [23-25]. Reportedly, declining engagement and attrition are the main barriers to the efficacy of digital health interventions [16,26].

The American Heart Association (AHA), a US charity devoted to CVD prevention, developed the Cholesterol CarePlan Web app for patients prescribed a cholesterol-lowering medication. This Web app delivered to patients on their smartphones through the internet aims to increase patients’ awareness of the benefits associated with compliance with medication, regular physical activity, and a healthy diet while monitoring these behavioral risk factors over time. The Cholesterol CarePlan is a 12-week care plan for self-management of cholesterol focusing on lifestyle and medication compliance, with weekly reminders and educational videos designed using evidence-based guidelines such as AHA’s CVD risk, cholesterol, and lifestyle guidelines [13,27,28]. Using 7 health factors and lifestyle behaviors that support heart health, it is based on the AHA’s “ideal cardiovascular health.” These factors and behaviors, called “Life’s Simple 7,” are smoking status, healthy diet, physical activity, healthy weight, blood pressure, cholesterol, and blood glucose. Improvements in these 7 areas can increase the quality of life and lifespan [29]. The Web app is simple to use, comes from credibly sourced information, contains educational information including benefits of behavioral change, real-time tracking of biometric data, and may be self-administered by patients in consultation with their health care providers. The feasibility, acceptability, and efficacy of the AHA Cholesterol CarePlan have not been assessed among patients.

### Aims and Objectives

The main aim of this work is to establish whether the AHA Cholesterol CarePlan may be administered to patients as a Web app to improve cholesterol management and lifestyle among patients prescribed a cholesterol-lowering medication. The primary study objectives are to evaluate the feasibility and acceptability of the AHA Cholesterol CarePlan delivered as a Web app. The secondary objectives are to evaluate the Web app’s efficacy.

## Methods

### Study Design

This is a prospective, observational feasibility study involving the use of a Web app on a smartphone for 24 weeks along with the collection of clinical measurements in general practice at baseline and 12 and 24 weeks after the Web app administration.

### Sample Size

This study will aim to recruit 180 patients to participate in the study and come for clinical assessments. A formal power calculation for the sample size was not conducted as this project was funded as a feasibility study. Therefore, sample size estimates are not required.

### Exclusion Criteria

Patients not currently being prescribed cholesterol-lowering medication or being prescribed for <30 days prior to being invited to take part in the study will be excluded. In addition, patients not owning a smartphone, unable to consent to research, and having insufficient command over English will be excluded. The capacity of participants will be monitored by a health care professional during 3 clinic visits. Individuals who lose capacity during the course of the study will also be excluded.

### Setting and Site Selection

The National Institute for Health Research (NIHR) Clinical Research Network North West London will contact research active practices with the goal of setting up to 14 general practices for research across North West London. Research active practices are defined as practices with a previous record of carrying out research activities.

### Participant Enrollment

To participate in the study, potentially eligible patients will be identified from the general practice databases by administrative staff at each participating general practice using automated eligibility search pertaining to prescribed medication. To maximize recruitment, patients will be invited by post, SMS text messaging, and opportunistically. General practices using post and text invitations will invite patients to come to prescheduled appointments. Practices inviting patients opportunistically will invite patients as part of routine clinical care. Patients will be invited in the order of acceptance until 180 patients come into their first visit.

Patients invited by post will be mailed study materials (invitation and patient information sheet) by general practice administrative staff. Opportunistically recruited patients will be invited by their health care professionals and receive study materials in paper copy. Finally, patients invited by SMS text messaging on their mobile phones by general practice administrative staff will receive study materials electronically. Patients who decide not to participate will be given an option to complete an anonymous sociodemographic survey either in paper copy with a prepaid envelope (if invited by post or opportunistically) or using a weblink to a Web-based Qualtrics survey (if invited by SMS text messaging). There will be no financial incentives for study participation.

### Data Collection

The sociodemographic survey containing information on comorbidities (stroke, heart disease, hypertension, familial hypercholesterolemia, kidney disease, type 2 diabetes, and dementia), age, gender, ethnicity, education, partial postcode, and smartphone ownership will be collected among study participants through the Web app. In addition, sociodemographic data (not including smartphone ownership or education) for study participants will be obtained from their medical records by general practices. Among consenting nonparticipants, the sociodemographic survey will be administered anonymously (with no possibility of further data linkage) either using a paper or a Web-based survey. All potentially eligible patients will not be asked to respond to the sociodemographic survey. Instead, anonymous sociodemographic data will be obtained from these patients’ medical records by general practices. The number of invited individuals will be recorded by the general practice staff. Medication adherence at weeks 1, 12, and 24 will be collected from secondary data.

During the baseline visit, health care professionals will set up participants to use the Web app from their work computer with the internet using a prespecified Web address on a clinician interface of the Web app. During 20-minute consultations at weeks 1, 12, and 24, a health care professional will take and input clinical measurements (blood pressure, height, weight, smoking, and nonfasting cholesterol) into the clinician interface of the Web app (see Multimedia Appendix 1).

The Web app will send out an invitation to patients’ smartphone. Patients will be asked to log in and respond to the sociodemographic survey during baseline visit and medication adherence questions during 3 clinic visits. All other questions will be completed outside clinic. The AHA Cholesterol CarePlan consists of 12 weekly components. This includes Life Simple 7 questions; 12 weekly questionnaires pertaining to diet, physical activity, and taking of medication; 12 self-reported weight and blood pressure readings; 9 educational videos; and a Patient Satisfaction Survey. This is a total of 76 multiple choice questions (46 unique questions) and 9 videos (6 unique videos). In addition, the following questionnaires will be administered through the Web app: sociodemographics, Technology Readiness Index (TRI) [30], System Usability Scale (SUS) [31], Medication Adherence Rating Scale (MARS) [32], and Short-Form Health Survey (SF-12) [33]. This is a total of 99 multiple choice questions (55 unique questions). It should take a patient 5-15 minutes to complete questions on a weekly basis. Patients will have a week to answer each week’s questions and may resume at a later time. Patients will be sent electronic reminders to complete weekly questions and book follow-up consultations (see Multimedia Appendix 2).

No equipment will be provided for self-monitoring of blood pressure and weight, and these questions will be optional. Multimedia Appendix 3 shows a timeline of quantified assessments recorded through the Web app.

Among patients who may choose not to complete the CarePlan, the questionnaires including sociodemographics, TRI, SUS, MARS, SF-12, and Patient Satisfaction will be administered through a Web-based Qualtrics survey after 12 weeks. These patients will be asked to complete sociodemographic and MARS in clinic and all other questions outside clinic. In addition, the MARS and SF-12 will be administered after 24 weeks through a Web-based Qualtrics survey. Patients will be asked to complete the MARS in clinic and the SF-12 outside clinic. Patients will have a week to complete these questions.

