### Statistical Analysis

The feasibility of administering the AHA Cholesterol CarePlan will be judged by recruitment and dropout statistics as well as by the sociodemographic and comorbidity profile of study participants in comparison with those of invited patients and all eligible patients. The participation rate will be judged as the percentage of people who consent to take part in the study out of all invited patients. General descriptive statistics will describe the sociodemographics and comorbidities of (1) consenting study participants; (2) consenting nonparticipants; and (3) all potentially eligible study patients. Invited patients will be described in terms of self-reported smartphone ownership. This will inform the likely generalizability of subsequent findings.

Compliance with the Web app will be measured using the frequency and duration of use. Patients’ weekly participation in the Web app will be automatically tracked, as well as whether they download educational videos. Compliance with the Web app will be measured using the number of weekly questionnaires attempted, the number of questions completed, and the number of educational videos downloaded. Furthermore, compliance will be described as a percentage of content accessed out of all content presented through the Web app throughout the 12-week care plan, as well as on a weekly basis.

It is anticipated that patients may be grouped into full compliers if they complete 12 weeks, good compliers if they complete 8 weeks, poor compliers if they complete 1-7 weeks, and noncompliers if they do not complete any of the weekly AHA Cholesterol CarePlan questions. Among compliers with the Web app, medication persistence and changes in diet and physical exercise will be examined throughout the 12-week Cholesterol CarePlan, and changes in the quality of life, self-reported medication adherence will be assessed at weeks 1, 12, and 24. In addition, the self-reported quality of life will be assessed using the Short-Form Health Survey [33]. The self-reported behavioral change in relation to diet and physical exercise, as well as medication persistence, will be assessed through weekly questions in the AHA Cholesterol CarePlan. Furthermore, self-reported adherence to cholesterol- lowering medication will be examined using the MARS [32].

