The acceptability of the Cholesterol CarePlan will be assessed using patients’ readiness to embrace new technologies, the usability of the Web app, and patient satisfaction. Patients’ behavior in relation to readiness to adopt new technology will be examined using the 12-item TRI [30]. The Web app usability will be assessed using the 10-item SUS [31]. Furthermore, patient satisfaction with the Cholesterol CarePlan will be assessed using a questionnaire developed by the AHA.

The efficacy of the Cholesterol CarePlan will be judged by examining the Web app compliance with changes in medication adherence and clinical risk factors. Medication adherence will be collected from secondary data using the Medication Possession Ratio and Proportion of Days Covered. These measures are based on the number of days medication supplied and the quantity of medication dispensed for each filled prescription [34,35]. A difference-in-difference (DID) analysis using multiple linear regression, controlling for education, socioeconomic deprivation, ethnicity, gender, and age will be performed. Using DID, a time-series average change in medication adherence, cholesterol, smoking, blood pressure, and body mass index over 3 time-points will be compared among full compliers and partial compliers, respectively, with Web app noncompliers. Interactions in regression models will be explored using explanatory variables. In addition, subgroups analyses (by education, socioeconomic deprivation, ethnicity, gender, and age) will explore differences in medication adherence and clinical outcomes among full compliers, partial compliers, and noncompliers with the Web app. Finally, using multiple regression modeling while controlling for education, socioeconomic deprivation, ethnicity, gender and age, average changes in diet, physical exercise, and quality of life will be examined among Web app compliers.

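### Patients book their week-12 and week-24 visits in response to electronic reminders, so visit-based outcomes may be differentially missing among app noncompliers, the reference group

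*Protocol article*

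**What the plan says.** All references are to the Methods of the protocol article.

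- **Booking.** Data Collection: "Patients will be sent electronic reminders to complete weekly questions and book follow-up consultations". The sentence points to Multimedia Appendix 2 (the patient pathway), which is not shown. For the first visit, Participant Enrollment describes a different arrangement: "General practices using post and text invitations will invite patients to come to prescheduled appointments".
- **What needs a visit.** Data Collection says that at weeks 1, 12 and 24 "a health care professional will take and input clinical measurements (blood pressure, height, weight, smoking, and nonfasting cholesterol"). The Medication Adherence Rating Scale (MARS) is also to be answered in clinic.
- **What does not.** Data Collection: "Medication adherence at weeks 1, 12, and 24 will be collected from secondary data". Statistical Analysis names the Medication Possession Ratio and Proportion of Days Covered (MPR/PDC) as these measures.
- **Patients who do not complete the CarePlan.** Their questionnaires "will be administered through a Web-based Qualtrics survey after 12 weeks", with the MARS and SF-12 again after 24 weeks. They are still asked to do the MARS in clinic.
- **Reference group.** Statistical Analysis classes patients as "noncompliers if they do not complete any of the weekly AHA Cholesterol CarePlan questions". Changes over three time-points "will be compared among full compliers and partial compliers, respectively, with Web app noncompliers".
- **Practice records.** Data Handling and Security describes a practice extract on prescribed medication, and Data Collection adds sociodemographic data from records. Neither names cholesterol, blood pressure, weight or smoking from the record.

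**The concern.** A reminder to book implies that the appointment has not yet been made and that the patient has to act. Noncompliers are, by definition, patients who acted on none of the prompts for weekly questions. If the prompt to book is of a similar kind, they are plausibly the patients least likely to respond to it. The exposure under study (app engagement) and the chance of having a follow-up value would then be linked by design.

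Four of the five DID outcomes need a visit: cholesterol, smoking, blood pressure and body mass index. The fifth, medication adherence, does not. The in-clinic MARS is exposed in the same way. Loss concentrated in the reference group costs precision where it is probably scarcest. It also biases the contrast if noncompliers who attend differ in their change from those who do not. A visit that did not happen cannot be recovered by analysis unless another source for the value was arranged.

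**Working it through.** The plan has no figure to reproduce: 180 is a recruitment target without a power calculation, and no attendance, dropout or compliance-group rate is given. Every rate below is an assumption used only to show scale.

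**1. Precision, one scenario**

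Assumed: 60 full compliers, 30 noncompliers, SD of change in cholesterol 0.8 mmol/L in both groups. SE = 0.8 × √(1/n₁ + 1/n₀).

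| Attendance | n₁, n₀ | SE (mmol/L) |
|---|---|---|
| Everyone attends | 60, 30 | 0.8 × √(1/60 + 1/30) = 0.179 |
| 69 of 90, equal rates (76.7%) | 46, 23 | 0.8 × √(1/46 + 1/23) = 0.204 |
| 69 of 90, unequal (90% and 50%) | 54, 15 | 0.8 × √(1/54 + 1/15) = 0.233 |

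The step from full to unequal attendance is √[(1/54 + 1/15)/(1/60 + 1/30)] = 1.31. Full attendance is not a realistic comparator, because some loss occurs however visits are booked. The part due to attendance being unequal is 0.233/0.204 = 1.14, about 14%. The rest is ordinary attrition.

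**2. Precision over a range**

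Assumed: noncompliers 10-30% of 180 (18 to 54 patients), full compliers 30-50% of 180 with 90% attending (48.6 to 81). Minimum detectable difference in SD units, two-sided 5% level, 80% power: (1.96 + 0.84) × √(1/n₀ + 1/n₁).

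| Noncomplier attendance | n₀ | Detectable difference (SD) |
|---|---|---|
| 100% | 18 to 54 | 0.77 to 0.49 |
| 40% | 7.2 to 21.6 | 1.12 to 0.68 |

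These are simple two-group comparisons of change, without covariates. They include ordinary loss as well as differential loss.

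**3. Bias**

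Complete-case bias in a group mean = (1 − attendance) × gap in mean change between attenders and non-attenders.

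| Attendance | Gap 0.2 SD | Gap 0.5 SD |
|---|---|---|
| 90% | 0.1 × 0.2 = 0.02 | 0.1 × 0.5 = 0.05 |
| 70% | 0.3 × 0.2 = 0.06 | 0.3 × 0.5 = 0.15 |
| 40% | 0.6 × 0.2 = 0.12 | 0.6 × 0.5 = 0.30 |

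The bias in the reference mean is therefore 0.06 to 0.30 SD for 40-70% attendance. If the same gap held among compliers with 90% attending, the net bias in the contrast would be 0.06 − 0.02 = 0.04 to 0.30 − 0.05 = 0.25 SD. With equal attendance and equal gaps it would cancel, so it is the inequality that matters.

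In the scenario of step 1, a gap of 0.2 mmol/L and 50% attendance give 0.5 × 0.2 = 0.1 mmol/L in the reference mean, or 0.1/0.233 = 0.43 of the standard error.

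**The case against.** The strongest reply is that the text says less than a reader might infer. Several stronger readings are tempting and are not supported.

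- **One shared message, or reminders as the only route.** The article describes the two reminders together. It does not say that one message does both jobs, that the app sends the booking reminder, or that the practice never schedules or chases a visit. The appendix that may settle this is not shown, and practice staff already text patients at the invitation stage. This stands.
- **Patients who ignore the app will miss their visits.** That is a prediction. The article expects these patients in clinic for the MARS and gives them a questionnaire route outside the app. This stands as a limit on the claim. However, the survey route as described carries no clinical measurements, and asking for attendance does not secure it.
- **The whole reference group loses its data.** This is too broad. MPR/PDC need no visit, and the SF-12, technology readiness, usability and satisfaction questionnaires are completed outside clinic.
- **The dropout statistic is invalid.** Feasibility is judged partly by dropout, and retention under the delivery system actually used is a legitimate feasibility result. It is easier to interpret if attendance is shown by compliance group, but it is not wrong.

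Efficacy is also a secondary objective with no power claim, and missing-data methods may sit in a full protocol or analysis plan that is not at hand. Their absence is not counted here. What remains is a stated booking procedure with a foreseeable link to the exposure.

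**Conclusion.** The point holds as a foreseeable risk from a stated procedure. It is neither a contradiction nor a demonstrated loss. Follow-up attendance may correlate with app engagement, so cholesterol, blood pressure, body mass index, smoking and the in-clinic MARS may be differentially missing among noncompliers. MPR/PDC are not affected.

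The size cannot be fixed from the documents. The 14% rise in standard error rests on the assumed 60/30 split and 69 of 90 attending. The larger figure of 31% should not be attributed to the booking arrangement, because it is measured against full attendance. The bias range rests on assumed attendance and an assumed gap. If attending and absent noncompliers change alike, the bias is zero. The change is worth making because it costs little and must be made before the visits fall due.

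**What to change.** 1. Offer and book the week-12 and week-24 appointments for every participant at the baseline visit, which all attend in person. Have the practice send appointment reminders that do not depend on app use. If the patient pathway already provides for this, say so in the Data Collection section.
2. Report attendance at weeks 12 and 24 by compliance group, alongside the dropout statistics.
3. Extend the planned practice extract to routinely recorded cholesterol, blood pressure, weight and smoking within a stated window around each visit. Use these values for missed visits in a sensitivity analysis.

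The cost is two bookings per participant with some slots unused, and a slightly larger extract with the permissions it needs. Routine values are less standardised than study measurements, which is why they belong in a sensitivity analysis.
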